### Procedures and assessments

Patients will visit the outpatient clinic at screening, baseline, week 5, week 13, and every 12 weeks thereafter until study completion (weeks 25, 37, 49, 61, 73, 85, 97, 109, 121, 133, 145) (Table 1). A variety of parameters will be collected during each visit to assess efficacy, including physician- (PASI/IGA (static; scale 0–4 [30])) and patient-reported (patient-reported global assessment (PGA static; scale 0–4)) outcomes. Quality of life assessment will be performed using Skindex and DLQI questionnaires. Safety will be assessed by evaluating the incidence of (serious) adverse events, obtaining a detailed medical history, thorough physical examination, vital signs, clinical laboratory testing, and urinalysis (including pregnancy tests for females of childbearing potential at screening). Concomitant medication and medical procedures will be collected from obtainment of informed consent up to end of study. Patients will receive a diary in which they will register the administration dates of adalimumab (and MTX in the combination group), any changes in their health status, and/or changes in concomitant medication used. The local investigator reviews the diary to determine drug adherence and the incidence and type of adverse events. An independent Data Safety Monitoring Board (DSMB) has been established to review efficacy and safety data periodically in an unblinded fashion.

### Laboratory testing

Blood samples will be collected at each visit (serum samples are collected just before administration of adalimumab (3-day window) to ensure accurate determination of serum through levels) to monitor drug safety, to determine immunogenicity against adalimumab, and to measure adalimumab serum through levels. Samples for serum preparation are kept at room temperature for 1–2 hours for coagulation, followed by centrifugation at 3000 RPM for 15 minutes at room temperature. Supernatant is collected, aliquoted, and stored at −20 °C until further use. Adalimumab serum through levels will be determined using a non-commercial enzyme-linked immunosorbent assay (ELISA, Sanquin, Amsterdam, The Netherlands). Detection of anti-adalimumab antibodies will be performed through a radioimmunoassay (Sanquin). The antibody test will be considered positive when the antibody concentration exceeds 12 AU/mL. Concentrations between 12 and 100 AU/mL will be considered low antibody titers; those above 100 AU/mL will be considered high antibody titers [3].

Additionally, a single blood sample will be collected at screening from which DNA will be collected and stored at −80 °C. As scientific interest in this field is currently increasing, DNA analysis will be performed based upon accumulating data acquired from (ongoing) pharmacogenetic studies.

### Justification of sample size

A total of 84 patients (randomized 1:1 to concomitant MTX or no MTX) will give the study at least 80% power at a 0.05 two-sided significance level using a two-sample chi-squared test to detect a difference of 28% in drug survival at week 49. We aim to enroll 93 patients to allow for an approximate 10% loss to follow-up. These calculations were performed using Nquery 6.0.2. Due to the lack of data in a psoriasis population, the expected clinically relevant difference in drug survival between both treatment groups was hypothesized based on studies performed in patients with RA. The prevalence of (clinically relevant) anti-drug antibody formation is estimated to be 45% in patients on adalimumab monotherapy (a similar percentage is found in patients with psoriasis [31] and around 17% in patients on adalimumab with low-dose (5–10 mg) MTX after 49 weeks [32]. A clear correlation between antibody formation and treatment failure (with subsequent treatment discontinuation) in patients on adalimumab has been demonstrated [31]. Based on these data, drug survival is estimated to be 83% (100 minus 17) for the experimental group and 55% (100 minus 45) for the control group after 49 weeks of follow-up.

### Statistical analysis

The primary analysis will be conducted on the intention-to-treat population, including all randomized participants in the groups to which they were randomized. A per-protocol population (excluding major protocol violations) will be used to check the robustness of the primary analyses. The safety population will consist of all patients receiving at least one dose of the study drug.

Adverse events will be coded according to the Medical Dictionary for Regulatory Activities (MedDRA) adverse event classification. The overall incidence of (serious) adverse events and number and proportion of patients reporting such events will be summarized by treatment group.

Differences in dichotomous outcomes among the two study groups will be analyzed using the chi-squared test or Fisher’s exact test when the expected cell frequencies fall below 5. We will express differences in drug survival as absolute differences and relative risks, with associated 95% confidence intervals, with the group on adalimumab monotherapy as the reference. In case patients are lost to follow-up during the study period, we will analyze these data by means of survival analysis. We will construct cumulative survival curves (Kaplan-Meier method) for the treatment groups, and these curves will be compared using the log-rank test. One-way analysis-of-variance statistics will be calculated to compare continuous outcome measures between groups.

There are no formal planned interim analyses, but progress reports on all data issues are presented to the DSMB.

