### Endpoints

The primary outcome is adalimumab drug survival (number of patients still on adalimumab treatment) at week 49.

Secondary outcomes are the following:Adalimumab drug survival (number of patients still on adalimumab treatment) at week 145Proportion of patients who reach treatment goals^1^ at week 13, week 25, week 49, and week 145Proportion of patients achieving PASI 75 at weeks 49 and 145Proportion of patients achieving IGA clear or almost clear at weeks 49 and 145Mean improvement in PASI at weeks 49 and 145Proportion of patients with PGA clear or almost clear at weeks 49 and 145Mean improvement in Dermatology Life Quality Index (DLQI) and Skindex at weeks 49 and 145Proportion of patients with (serious) adverse events at weeks 49 and 145Proportion of patients with changes in laboratory assessments at weeks 49 and 145Proportion of patients with (no, low, or high) levels of antibodies at weeks 49 and 145Median adalimumab trough concentrations (mg/L) at weeks 49 and 145Correlation between genetic polymorphisms and adalimumab response

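### Adverse events are compared only as crude proportions although the plan expects unequal time on adalimumab; if events are not collected after stopping, equal rates could look like excess harm from the combination

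*Protocol article*

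**What the plan says.** The Endpoints section lists, as a secondary outcome, the proportion of "patients with (serious) adverse events at weeks 49 and" 145. The Statistical analysis section adds: "The overall incidence of (serious) adverse events and number and proportion of patients reporting such events will be summarized by treatment group". It then assigns dichotomous outcomes a chi-squared test, or Fisher's exact test when expected cell counts are below 5. The safety population is everyone with at least one dose of study drug. Person-time, an on-treatment window and time to first event are not mentioned for safety. Kaplan-Meier and log-rank methods appear only after the sentence on drug survival, for patients lost to follow-up.

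On expected time on treatment, Justification of sample size says "drug survival is estimated to be 83% (100 minus 17) for the experimental group and 55% (100 minus 45) for the control group" at 49 weeks. Under Interventions, methotrexate starts two weeks before adalimumab, in the combination arm only.

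On how long events are collected, Table 1 schedules adverse events at study visits and has an early termination column. Procedures and assessments gives an end point (end of study) for collecting concomitant medication and procedures, but none for adverse events. Interventions bars systemic psoriasis drugs other than study medication throughout the study.

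**The concern.** A proportion ever having an event by a fixed week depends on the event rate and on how long each patient is watched. The primary hypothesis is that combination patients stay on adalimumab longer. If watching stops when adalimumab stops, the arm that does better on the primary outcome has more time in which to report an event. The crude comparison would then lean against the combination even if methotrexate added no risk.

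Safety of the combination is a stated aim, and the Background names serious infections and malignancies as the theoretical worry. A success on drug survival could bring an apparent safety penalty with it, and the planned tables give the reader no means of separating the two.

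**Working it through.** **1. The plan's own figure.** Inputs from Justification of sample size: 83% versus 55%, 80% power, two-sided 0.05, chi-squared test. With pooled variance and no continuity correction,

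n per arm = [1.96·√(2·0.69·0.31) + 0.8416·√(0.55·0.45 + 0.83·0.17)]² / 0.28² = (1.282 + 0.525)² / 0.0784 ≈ 41.6, so 42 per arm and 84 in total.

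This matches the plan; power at 42 per arm is 80.4%. The target of 93 follows from 84 × 1.10 = 92.4 (84/0.90 would give 94). The sample size is not in question. The check only confirms that 83% and 55% are the retention figures on which the trial is built.

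**2. Mean time on adalimumab to week 49.** The article does not give the shape of discontinuation, so a constant hazard is assumed: h = −ln(S)/49.

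- Combination: h = −ln(0.83)/49 = 0.00380 per week
- Monotherapy: h = −ln(0.55)/49 = 0.01220 per week

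Mean time = (1 − e^(−hT))/h.

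- Combination: 0.17/0.00380 = 44.7 weeks
- Monotherapy: 0.45/0.01220 = 36.9 weeks
- Ratio 1.21, a gap of about 8 weeks

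Other shapes:

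- Linear loss: 49·(1.83/2) = 44.8 versus 49·(1.55/2) = 38.0, ratio 1.18
- All stops at week 25: 44.9 versus 38.2, ratio 1.18
- All stops at week 13: 13·0.17 + 49·0.83 = 42.9 versus 13·0.45 + 49·0.55 = 32.8, ratio 1.31

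Adding the two-week methotrexate lead-in to the constant-hazard case gives 46.7/36.9 = 1.27.

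**3. Week 145 (extrapolation).** The article gives no retention at week 145. Carrying the same hazards forward implies 58% versus 17% still on drug, and mean times of 111.5 versus 68.0 weeks, ratio 1.64.

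**4. Effect on the crude proportion.** The article gives no event rate, so a range of 0.1 to 2 per patient-year is assumed, equal in both arms. Events are counted only while on adalimumab, and stopping is treated as independent of events. With m = rate/52,

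P(event) = m/(m + h) · (1 − e^(−(m + h)T)).

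| Rate per patient-year | Week 49, combination vs monotherapy | RR | Week 145, combination vs monotherapy | RR |
|---|---|---|---|---|
| 0.1 | 8.2% vs 6.8% | 1.21 | 18.9% vs 11.9% | 1.60 |
| 0.5 | 34.5% vs 28.9% | 1.19 | 61.4% vs 42.2% | 1.46 |
| 1 | 56.5% vs 48.1% | 1.18 | 80.5% vs 60.5% | 1.33 |
| 2 | 79.5% vs 69.6% | 1.14 | 90.8% vs 75.9% | 1.20 |

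The true rate ratio is 1.00 in every row, and an exposure-adjusted comparison targets that value.

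**5. Chance of a false signal.** If the chi-squared rule for dichotomous outcomes is applied to these proportions with 42 per arm, a normal approximation gives a probability of wrongly finding significant excess in the combination arm of about 14% to 52% at week 145 over these rates, against a nominal 2.5% in that direction. At week 49 it is about 4% to 18%.

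**6. The opposite case.** If every patient is followed to the fixed week at the same rate, the proportion is 1 − e^(−mT) in both arms. At 1 per patient-year and week 49 that is 61.0% in each arm, RR 1.0. The artefact depends wholly on the collection window.

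**The case against.** The strongest objection is that the premise is not in the document. A reader might infer from Table 1 that adverse events stop being recorded when adalimumab stops. The article has an early termination column but neither defines it nor says that follow-up ends there, and with complete follow-up and equal rates there is no bias. This stands, and it makes the point conditional. The ban on other systemic psoriasis drugs makes continued follow-up after stopping less likely, but that is inference.

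A reader might also conclude that combination patients are treated far longer. At week 49, the only time with a stated retention, the gap is about 8 weeks. At the lowest assumed rate the shift is 1.4 percentage points, or 0.014 × 42 ≈ 0.6 of a patient per arm. The larger week-145 figures are extrapolated. Both limits stand.

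Exposure-adjusted tables are often left to a statistical analysis plan, and the undefined term overall incidence might mean a rate. This stands in part. The Endpoints section, however, does not leave the measure open: it names the proportion at two fixed weeks.

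Finally, the proportion with an event by a fixed week is a legitimate description of a treatment strategy. A rate per patient-year assumes a roughly constant hazard, stopping for safety reasons is not independent of events, and events during the methotrexate lead-in are real, not spurious. This argues against replacing the crude proportions. It does not argue against putting an exposure-based measure beside them.

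**Conclusion.** The point holds in conditional form. The plan fixes a crude proportion as its safety measure while expecting unequal time on adalimumab, and it does not say whether events are counted after adalimumab stops. If they are not, equal rates could give a spurious relative risk of about 1.14 to 1.21 at week 49 and 1.20 to 1.60 at week 145. If all patients are observed to the fixed week at equal rates, it is 1.0.

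These sizes rest on the plan's 83% and 55%, a constant discontinuation hazard (exposure ratio 1.18 to 1.31 at week 49 under the other shapes tried), assumed event rates of 0.1 to 2 per patient-year, and stopping independent of events. Week 145 also rests on extrapolated retention. The effect is modest at week 49 and potentially misleading at week 145. The documents do not support saying that the safety comparison is biased as it stands; they support saying that it cannot be interpreted until the collection window is stated and exposure is shown.

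**What to change.** Three changes, before the safety data are compared by arm:

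1. State whether adverse events are collected and counted after a patient stops adalimumab and, if so, until when.
2. Keep the crude proportions. Beside them, compare (serious) adverse events by arm as events per 100 patient-years, from first study drug (methotrexate lead-in included) to end of observation, with a rate ratio and 95% confidence interval.
3. Add a time-to-first-event analysis (cumulative incidence) for serious adverse events, above all at week 145.

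The cost is a few sentences and one extra table, plus the curve. The diary already records administration dates and health changes, so no new data collection is needed for on-treatment exposure. The drawback is that the rate assumes a roughly constant hazard; the cumulative-incidence curve lets readers check that. The sample size does not change.

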### Randomization and blinding

Consecutive patients will be prospectively enrolled and randomly assigned if eligible to either the intervention (adalimumab with MTX) or control (adalimumab monotherapy) group after obtaining informed consent. Each consecutive patient will be assigned a randomization number according to a computer-generated randomization list (ALEA) using random block sizes of 2, 4, 6, and 8 to ensure allocation concealment. Randomization is stratified for TNFα-blocker exposure status to achieve balance with regard to prior TNFα-blocker exposure in the study population.

This is an observer-blinded study. The observer (outcome assessor) will perform clinical outcome assessments of disease severity (Psoriasis Area and Severity Index (PASI) and investigator global assessment (IGA)) at each study visit. The clinician performs all other study procedures and is not blinded. Both clinician and participant know the treatment allocation; as such, no special measures are required to allow for breaking of treatment codes. However, treatment allocation will not be revealed to the recruiting physician until participants’ details and key stratification variables have been irrevocably entered onto the web-based randomization site.

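### Randomisation is stratified by prior TNFα-blocker exposure, but none of the tests named in the analysis section uses that stratum; the tests stay valid, and become somewhat conservative if exposure is prognostic

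*Protocol article*

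**What the plan says.** Under Randomization and blinding, the protocol article states: "Randomization is stratified for TNFα-blocker exposure status to achieve balance with regard to prior TNFα-blocker exposure in the study population". This is the only stratification factor named.

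Under Statistical analysis, the methods for comparing the groups are:
- Binary outcomes, including drug survival: "Differences in dichotomous outcomes among the two study groups will be analyzed using the chi-squared test", or Fisher's exact test when expected cell frequencies are small. Drug survival is also reported as an absolute difference and a relative risk with 95% confidence intervals.
- Drug survival when patients are lost to follow-up: Kaplan-Meier curves, and "these curves will be compared using the log-rank test".
- Continuous outcomes: one-way analysis of variance, which has treatment group as its only factor.

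The Justification of sample size uses the same kind of test. It claims "at least 80% power at a 0.05 two-sided significance level using a two-sample chi-squared test" from 84 patients, on the expectation that "drug survival is estimated to be 83% (100 minus 17) for the experimental group and 55% (100 minus 45) for the control group".

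**The concern.** Stratified randomisation forces the arms to be alike on the stratum. If the stratum predicts outcome, part of the outcome variation can then no longer contribute to chance differences between arms. A test that ignores the stratum still counts that variation in its standard error. The standard error is then larger than the true sampling variation, the type I error falls below the nominal 5%, and some power is given away.

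At stake is efficiency, together with agreement between design and analysis. The planned power has little slack, and the article describes recruitment as difficult (36 randomised of 93 wanted, three hospitals added), so precision that can be had without enrolling anyone is worth taking.

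**Working it through.** **Inputs from the protocol article.** Week-49 drug survival 83% (combination) and 55% (monotherapy); two-sided alpha 0.05; power at least 80%; 84 patients at 1:1, so 42 per arm; random blocks of 2, 4, 6 and 8 within strata.

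**Assumptions, because the article is silent.** Share previously exposed to a TNFα blocker: 20%, 35% or 50%. Odds ratio (OR) of prior exposure for drug survival: 1, 0.5, 0.33 or 0.2, the same in both arms. Stratum rates are set so that the arm averages stay at 55% and 83%.

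**Step 1: the plan's own figure.** With average rate 0.69:

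n per arm = [1.96·√(2·0.69·0.31) + 0.842·√(0.83·0.17 + 0.55·0.45)]² / 0.28² = [1.96·√0.4278 + 0.842·√0.3886]² / 0.0784 = 41.6, so 42 per arm and 84 in total.

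Power at 42 per arm = Φ[(0.28 − 1.96·√(0.4278/42)) / √(0.3886/42)] = 80.4%.

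The stated sample size therefore reproduces with the unstratified test.

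**Step 2: power with the stratum used.** The two variances are replaced by their within-stratum averages, weighted by share. Example with share 50% and OR 0.33: monotherapy rates are 0.684 (unexposed) and 0.416 (exposed); combination rates are 0.904 and 0.756.
- Within-stratum variance sum: 0.5·(0.684·0.316 + 0.904·0.096) + 0.5·(0.416·0.584 + 0.756·0.244) = 0.365, against 0.389 unstratified.
- Standard-error ratio, unstratified to stratified: √(0.3886/0.3652) = 1.03.
- Null variance, from the stratum averages 0.794 and 0.586: 0.5·2·0.794·0.206 + 0.5·2·0.586·0.414 = 0.406.
- Power = Φ[(0.28 − 1.96·√(0.406/42)) / √(0.365/42)] = 82.5%.

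Over the assumed range:

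| OR of exposure | Stratified power (unstratified formula 80.4%) | Gain, points | SE ratio | Simulated gain, same trials, points |
|---|---|---|---|---|
| 1 | 80.4% | 0 | 1.00 | about 0 |
| 0.5 | 81.0-81.2% | 0.6-0.8 | 1.01 | 0.3-0.5 |
| 0.33 | 82.0-82.5% | 1.6-2.1 | 1.02-1.03 | 1.1-1.4 |
| 0.2 | 83.7-84.7% | 3.3-4.3 | 1.05-1.07 | 2.1-3.0 |

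The last column is from 8,000 simulated trials per case with the article's block sizes, with the unstratified chi-squared and the CMH test applied to the same data. It is a little smaller because the unstratified test also benefits from the balance that stratification brings (for example 82.9% against 85.2% at OR 0.2, share 50%). The half-width of the 95% interval for the risk difference is 18.9 points unstratified; stratified, it runs from 18.9 (OR 1) down to 17.7 (OR 0.2, share 35-50%).

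**Step 3: type I error.** With 69% survival in both arms, half the patients exposed, and a gap g between strata, the true standard error is the unstratified one times √(1 − (g²/4)/0.2139), where 0.2139 = 0.69·0.31.
- g = 20 points (OR about 0.38): factor 0.976, type I error 2·[1 − Φ(1.96/0.976)] = 4.5%.
- g = 30 points (OR about 0.22): factor 0.946, type I error 3.8%.
- g = 40 points (OR about 0.12): factor 0.902, type I error 3.0%.

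Simulation with 200,000 trials per case gave 4.5%, 3.9% and 3.0%, with CMH at about 5% throughout. In the block-randomised simulation (shares 20% and 50%), unstratified type I error was 5.2-5.3% at OR 1, 4.5-4.6% at OR 0.33 and 3.6-4.3% at OR 0.2; CMH stayed at 4.8-5.3%. Coverage of the unadjusted 95% interval was 94-96% in all cases.

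**The case against.** The strongest reply is that nothing stated is wrong. The trial is powered on an unstratified chi-squared test and analysed with one, the 80% is met, and type I error is not inflated. The stated reason for stratifying is balance only. No passage says that prior exposure predicts drug survival, or how many patients will have been exposed. The exposed share could also be small: the Trial status section notes that patients coming from another biologic often fall below the PASI 8 needed for entry. At an exposed share of 10-20% and an OR of 0.38 to 0.5, the simulated gain is under one power point. Finally, stratum adjustment is often left to an analysis plan, and that plan is not shown.

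Most of this stands, and it limits the point to efficiency and consistency. What does not carry is the appeal to the unseen plan. The article does not leave the methods open: it names a plain chi-squared test and a one-way analysis of variance, and the latter by definition excludes the stratum.

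A reader might infer more: that the omission certainly wastes power, that the confidence intervals are miscalibrated, or that the sponsor expected exposure to drive outcome. The documents support none of these. The loss depends on a prognostic effect they do not quantify, coverage stays at 94-96%, and the given motive is balance. Nor should a power gain be quoted for a 40-point gap between strata in both arms: around an 83% average at equal shares it would put one stratum at 83 + 20 = 103%.

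**Conclusion.** The mismatch is real: the one stratification factor appears in none of the named tests. The planned analysis remains valid and its 80% power at 84 patients holds. The cost is conditional on prior exposure being prognostic. With assumed exposed shares of 20-50% and a common odds ratio in both arms, the formula-based loss is:
- nil at OR 1;
- about 0.5 to 2 power points at OR 0.5 to 0.33;
- about 3 to 4 points at OR 0.2 (2 to 3 when both tests are simulated on the same trials), with intervals about 5-7% too wide.

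The error is always on the conservative side. This is a modest improvement worth making, not a threat to the trial's conclusions. The statement covers the named tests only; the genotype correlations have no named method.

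**What to change.** Pre-specify, with prior TNFα-blocker exposure as the stratum:
- for drug survival and the other binary outcomes, the CMH test with Mantel-Haenszel risk difference and relative risk and their 95% confidence intervals;
- where survival analysis is used, the stratified log-rank test;
- for continuous outcomes, a model with treatment and stratum as terms in place of the one-way analysis of variance.

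If an existing analysis plan already does this, the published description should be brought into line with it.

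The cost is a sentence or two of text. The stratum is already recorded at randomisation, the sample size need not change, and in simulation at OR 1 the two tests differed by no more than about 0.2 points in power or type I error. The change should be fixed before outcome data are compared by arm.
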